##### Change in Renal Function

We will observation renal function in at least 3000 patients before and after medication. The renal function indexes will include creatinine and blood urea nitrogen. To observe whether the above renal function indexes appear abnormal after medication, the diagnostic criteria for acute kidney injury will be defined based on the Kidney Disease: Improving Global Outcomes serum creatinine criteria [32] (at least 50% increase in creatinine within 7 days or a 26.5 μmol/L increase within 48 h).

The time frame for all four result items is 7 days (Table 2).

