### Monitoring Time and Follow-Up

Patients are monitored throughout the medication period in the hospital. The treatment duration of PDL for URTI ranges from 3 to 14 days. This study will include a follow-up period of 7 days after the completion of observation treatment [26], aiming to assess the drug’s long-term efficacy and observe any delayed ADRs. The follow-up will be conducted either through face-to-face meetings or via telephone communication. We will use systematic methods and reminders to schedule appointments with patients.

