#### Basic Information Form for Administering PDL

The researchers will record the AE information collected during the study period into the safety monitoring case report form (CRF). All patients will be required to complete CRF A (PDL basic information form). If the monitored patient experiences an ADR or AE during the medication period, the monitor will need to fill out CRF B. We will check the monitoring data; enter, encode, standardize, and clean the data; and then conduct a third-party data inspection. Any discrepancies in the data will be addressed by two data administrators who will resolve them after independently verifying the original CRFs.

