### Quality Control of ADRs

Each monitoring subcenter will formulate the first-level, quality-control rules and quality-control list according to the content of the monitoring program. The information system of each monitoring unit will be reviewed to ensure that the clinical study data are authentic and traceable. The implementation of the study will adhere to the research protocol and standard operating procedures in order to ensure the authenticity and reliability of the research data. The data collected are presented in Table 1.

**Table 1 table1:** Basic information form for administering Pudilan Xiaoyan oral liquid^a^.

Basic information	Before taking the medicine	After taking the medicine		
		7 days	14 days	21 days
Age	✓			
Sex	✓			
Smoking history	✓			
Occupation	✓			
Expense category^b^	✓			
Pathways to admission	✓			
Drinking alcohol	✓			
Western medicine diagnosis	✓			
Traditional Chinese medicine diagnosis	✓			
Past medical history	✓			
Personal history of allergies	✓			
Allergic manifestation	✓			
Previous other adverse drug reactions or events	✓			
Main drug combination: Western medicine, antibiotics, antipyretic analgesia, proprietary Chinese medicine, or other drugs		✓	✓	✓
Blood routine before and after treatment, white blood cell count, granulocyte, routine urine examination, liver function, renal function, ECG^c^ (test sheet within 30 days before treatment), C-reaction protein, influenza virus detection, pathogen detection, and other tests	✓	✓	✓	✓
Adverse reaction occurrence (yes or no)		✓	✓	✓

^a^Patients are visited and examined before and after taking the medication.

^b^Expense category refers to the classification of expenses, such as out-of-pocket (self-funded) costs, expenses covered by medical insurance, and other payment types. It helps in understanding how different types of expenses are categorized based on their funding source or payment method.

^c^ECG: electrocardiogram.

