### Outcome Measures

#### Primary Outcome Measure: Incidence of ADRs

The incidence of ADRs is the primary outcome measure, and we will identify factors that contributed to the occurrence of ADRs. The incidence of ADR will be primarily categorized in accordance with the criteria proposed by the Committee of International Organization of Medical Sciences: very common (≥10%), common (1%-10%, including 1%), occasional (0.1%-1%, including 0.1%), rare (0.01%-0.1%, including 0.01%), and very rare (<0.01%) [28], as well as according to the classification of ADR symptoms by the World Health Organization (WHO) [29]. The WHO classification of organs and systems involved in ADRs will also be referenced [30]. The incidence characteristics and regional distribution will be subsequently analyzed, while concurrently investigating the influencing factors (Table 2).

**Table 2 table2:** Centralized monitoring results of Pudilan Xiaoyan oral liquid in the registered hospitals.

Monitoring result	Description
Categorization	The ADR^a^ was categorized based on general, novel, and severe classifications The classification was based on the organs and systems affected by the ADR The symptoms of the ADR were classified
ADR incidence	The specific event features of each ADR included the incidence rates of various categories and whether they are infrequent or exceptionally rare
Pedogenic properties	Occurrence characteristics of ADRs specific to each category
Geographical distribution	The distribution of ADRs is primarily observed in North China, Central China, South China Each region exhibits distinct characteristics of ADRs
Influencing factors	Days of medication, age, drug combination, etc

^a^ADR: adverse drug reaction.

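### The 7-day time frame set for all four outcomes has no starting point and conflicts with the 10 to 21 days over which the primary ADR incidence is to be observed

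*Protocol article*

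**What the plan says.** All references are to the Methods of the protocol article.

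- Outcome Measures, primary outcome: "The incidence of ADRs is the primary outcome measure". No observation window is given there.
- Change in Renal Function, closing sentence: "The time frame for all four result items is 7 days (Table 2". The article has exactly four outcomes (ADR incidence, temperature normalization, liver function, renal function), so the primary is included. Table 2 lists categories of monitoring results and contains no time frame.
- Monitoring Time and Follow-Up: in hospital, monitoring covers all the time on drug. On course length the section states: "The treatment duration of PDL for URTI ranges from 3 to 14 days". A further week is then added once the drug has been stopped: "This study will include a follow-up period of 7 days after the completion of observation treatment". One stated purpose of that last week is to "observe any delayed ADRs".
- Table 1, under Quality Control of ADRs: the row "Adverse reaction occurrence (yes or no" is ticked at 7, 14 and 21 days after taking the medicine, as are the laboratory tests.
- The temperature outcome has its own 3-day period.
- Basic Information Form for Administering PDL: "If the monitored patient experiences an ADR or AE during the medication period, the monitor will need to fill out CRF B". The same paragraph opens more widely and has AE information from the whole study period entered in the case report form.

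**The concern.** An incidence has no meaning without a window. The article gives the primary outcome one window in the outcome section and a different one in the follow-up section and data schedule, and nothing reconciles them. An analyst who applied the 7 days literally from first dose would leave out an ADR on day 10 of a 14-day course. For any course of 7 days or more, the whole week added to detect delayed reactions would be left out as well.

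Three planned analyses depend on the answer:

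- ADRs are to be sorted into frequency bands by incidence, and a truncated numerator can move a reaction into a rarer band.
- Days of medication is a listed influencing factor, and a cut at day 7 removes the days on which longer courses differ from shorter ones.
- The nested case-control study draws controls from patients without ADRs. Under a 7-day definition, a patient with a day-10 ADR could serve as a control.

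**Working it through.** **Inputs.** Treatment lasts d = 3 to 14 days and follow-up is 7 days after treatment (Monitoring Time and Follow-Up). ADR status is collected at days 7, 14 and 21 (Table 1). The time frame is 7 days (Change in Renal Function).

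**The plan's own figure.** Longest observation = 14 + 7 = 21 days, which equals the last column of Table 1. Shortest observation = 3 + 7 = 10 days. The follow-up section and Table 1 therefore agree with each other, and the 7-day sentence is the one that does not fit.

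**Reading A: 7 days from first dose.** Share of observation kept = 7/(d + 7). Share of the post-treatment week kept = max(0, 7 − d)/7.

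| Course d | Planned observation | Kept | Lost | Post-treatment week kept |
|---|---|---|---|---|
| 3 | 10 days | 7/10 = 70% | 30% | 4/7 = 57% |
| 7 | 14 days | 7/14 = 50% | 50% | 0% |
| 14 | 21 days | 7/21 = 33% | 67% | 0% |

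Two of the three scheduled ADR assessments (days 14 and 21) lie outside this window.

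**Reading B: 7 days from last dose.** The delayed-ADR week is covered, but the d days on drug fall outside: 3/10 = 30%, 7/14 = 50% and 14/21 = 67% of planned observation.

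**Reading C: first dose to 7 days after last dose.** Nothing is lost. The sentence does not say this.

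**From time to events, Reading A only.** The documents give neither the distribution of course length nor the timing of ADRs. Assume that each whole-day length from 3 to 14 (12 values) is equally likely and that the daily hazard is low and constant. The share of ADRs in the window is then close to the share of at-risk days.

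- Hazard through the end of follow-up: days in window = 12 × 7 = 84. Days at risk = sum of (d + 7) = 102 + 84 = 186. Captured 84/186 = 45%, lost 55%.
- Hazard on drug only: days in window = sum of min(d, 7) = 3 + 4 + 5 + 6 + 8 × 7 = 74. Days at risk = sum of d = 102. Captured 74/102 = 73%, lost 27%.

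**The other windows.** The 3-day temperature period conflicts with a common 7 days whichever starting point is meant. The 7 days in the acute kidney injury criterion is the interval over which a creatinine rise is judged. It is not an observation period and gives no basis for a 7-day ADR window.

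**The case against.** The strongest reply is that no truncation is demonstrated. The sentence gives no starting point, and its 7 days match the length of the post-treatment follow-up, so the authors may have meant observation until 7 days after the end of treatment. The rest of the article fits that reading: patients are monitored through the whole medication period, causality grading has no day-7 limit, and ADR status is collected to day 21. Nowhere does the article say that ADRs after day 7 will be discarded. This stands, and it is why the losses above are conditional. It does not clear the sentence, which does not express that meaning and still contradicts the temperature period.

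It also stands that a share of observation time is not a share of ADRs, that two thirds applies only to a 14-day course counted from first dose, and that no passage supports a constant hazard for a week after the drug is stopped.

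Three stronger readings are tempting, and the documents do not support them:

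- *The plan discards up to two thirds of its observation.* This holds only under a first-dose start, which the sentence does not state.
- *Counting from last dose would be worse.* This is not shown. By observation time, a 3-day course loses 30% under either start.
- *Events in the follow-up week get no CRF B and so no details for causality grading.* The form's trigger names the medication period but does not say that it applies only then. The same paragraph takes in AE information from the whole study period, and CRF B itself is not shown. The wording needs aligning, but it does not prove that such events go undocumented.

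**Conclusion.** The concern holds as a contradiction in the definition of the primary outcome. The article states a 7-day frame for ADR incidence, so this is not a detail left to a fuller document, and the frame conflicts with the article's own follow-up plan and schedule. Its starting point is missing and the table it cites does not support it.

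The size depends on the reading. From first dose, 30% to 67% of planned observation is lost, and incidence can only go down. The 27% to 55% of ADRs missed is illustrative and rests on uniform course lengths and a constant hazard. From last dose, on-treatment ADRs are outside. Under first dose to 7 days after last dose, the loss is zero. Because this is the only primary outcome and the literal wording can change its value, the window should be settled before the analysis.

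**What to change.** 1. Replace the closing sentence of Change in Renal Function. State the primary ADR window as first dose to 7 days after last dose, which is day 10 to day 21 depending on course length. This agrees with the follow-up section and Table 1. Any incidence by day 7 can be reported as a secondary cut.
2. Give each secondary outcome its own window: the 3-day period already stated for temperature, and the scheduled tests in Table 1 for liver and renal function. Remove the reference to Table 2 or add the time frames to that table.
3. Reconcile the CRF B trigger with the wider wording in its own paragraph and with the follow-up period, so that AEs and ADRs in follow-up are documented well enough for causality grading.

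The cost is mainly a few sentences in the protocol and the form instructions, since the day 14 and day 21 assessments are already scheduled. Enrollment began in July 2019, so the sponsor should check whether follow-up events in patients already observed have a CRF B. The article does not show whether any are missing; if some are, those forms would have to be completed retrospectively.

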### Statistical Analysis

Data review and cleaning work will take the paper monitoring form as the original record, delete redundant and repetitive parts, supplement missing data, modify wrong values, and report about abnormal values. The basic characteristics of the patients will be included. Descriptive analyses will be performed for the primary and secondary outcomes. SPSS Statistics 26 software (IBM Corp) will be used for descriptive analysis. Data conforming to a normal distribution will be described by means and SDs, and those conforming to a skewed distribution will be described by median, minimum, maximum, and IQR scores. Categorical data will be described by frequencies and percentages. A cohort, nested, case-control study will be used. If 1 patient has an ADR, then 4 patients without ADRs will be matched as the control group according to gender, age with 5 years, drug batch, and other factors, at a ratio of 1∶4 to compare the symptoms related to adverse reactions. In addition, the risk factors of adverse reactions will be analyzed. First, the differences of ADR incidence among the possible influencing factors will be compared separately to find the factors with large differences. Then, synthetic minority oversampling technique and group least absolute shrinkage and selection operator methods will be used to identify factors influencing the occurrence of ADRs, while propensity scoring methods will be used to control for confounding variables.

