**Methods:**

The study is a prospective, observational, multicenter, hospital-based surveillance study. A total of 17 hospitals from China are involved. The study is expected to enroll a large sample of 10,000 patients aged between 18 and 80 years with upper respiratory tract infection who were prescribed PDL. The patients’ data, including demographics, medical history, diagnostic information, medication details, adverse events, and laboratory test results, will be monitored. The occurrence of ADRs will be recorded. The primary outcome is the incidence of ADR. Secondary outcomes are the ratio of patients whose body temperature return to the normal range (cases of body temperature normalization and the duration for achieving normal body temperature within a 3-day period will be documented) and changes in liver and kidney function (occurrence of drug-induced liver injury and acute kidney injury). Descriptive analyses will be performed for the primary and secondary outcomes. A cohort, nested, case-control study design will be used. If one patient has an ADR, then 4 patients without ADRs will be matched as the control group according to gender, age within 5 years, drug batch, and other factors, at a ratio of 1∶4 to compare the symptoms related to ADRs. The differences of ADR incidence among the possible influencing factors will be compared separately to find the factors with large differences. Then, synthetic minority oversampling technique and group least absolute shrinkage and selection operator methods will be used to identify factors influencing the occurrence of ADRs. Finally, propensity scoring methods will be used to control for confounding variables. The progress of each subcenter will be closely monitored, and the incidence of ADR will be systematically calculated. Furthermore, the characteristics and influencing factors of ADR will be analyzed, along with an investigation into its geographical distribution.

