### Interpretation of ADR Causality

In this study, AEs, ADRs, and serious ADRs will be judged according to the *Administrative Measures on Reporting and Monitoring for Adverse Drug Reaction* issued by the Ministry of Health in 2011 [27]. The evaluation of ADRs follows a 3-level decision-making process, comprising initial reporting by clinical practitioners, assessment by the Expert Committee for ADR Monitoring at the surveillance center, and final determination by panel of senior domestic experts. Based on established assessment criteria, the causal relationship between AEs and PDL will be evaluated according to five key parameters: (1) temporal plausibility, (2) consistency with known mechanisms of action or established adverse reaction profiles, (3) positive dechallenge response, (4) positive rechallenge response, and (5) exclusion of alternative explanations. The correlation between AE and PDL will be divided into six grades: positive, probable, possible, possibly unrelated, to be evaluated, and unable to be evaluated. Those judged to be the first three grades will be classified as ADRs, those judged to be “possibly unrelated” will be classified as AEs, and those judged as “to be evaluated” or “unable to be evaluated” should be rejudged in combination with the original monitoring data. We will conduct thorough evaluations to ultimately confirm the incidence of ADRs associated with PDL. This approach helps to minimize potential biases associated with patient self-reporting and variations in medical practices across different centers. The occurrence characteristics and processes of ADRs will be meticulously documented, with particular emphasis on the timing of ADR onset, the implementation time of intervention measures for ADRs, and the termination time of ADRs.

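### The stated purpose of the 1:4 matched controls, comparing ADR symptoms, is settled largely by how cases and controls are defined; the matched set should be assigned to factors preceding the ADR instead

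*Protocol article*

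**What the plan says.** The Statistical Analysis section announces a nested case-control study and sets the control rule: "If 1 patient has an ADR, then 4 patients without ADRs will be matched as the control group". Matching is on gender, age, drug batch and other factors, and the section gives the aim of the matched set as "to compare the symptoms related to adverse reactions". The Methods paragraph of the Abstract gives the same aim: "to compare the symptoms related to ADRs".

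In Statistical Analysis the risk-factor work follows as a further item: "In addition, the risk factors of adverse reactions will be analyzed". Its first step is that "the differences of ADR incidence among the possible influencing factors will be compared separately to find the factors with large differences". Variable selection and propensity scoring come after that. Neither place says which of these steps, if any, uses the matched set.

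Case status is defined under Interpretation of ADR Causality, from the six causality grades: "Those judged to be the first three grades will be classified as ADRs". The three grades are positive, probable and possible. For the next grade, "those judged to be “possibly unrelated” will be classified as AEs".

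On recording, the section on the basic information form says that if a monitored patient "experiences an ADR or AE during the medication period, the monitor will need to fill out CRF B".

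**The concern.** A case-control comparison is informative when the variable compared is distinct from the variable that defines the groups. Here the two are nearly the same: a patient becomes a case by having an event judged related to PDL, and the comparison is then of the symptoms of such events. The result follows from the definition, not from the data.

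Two things are at stake. A table of symptoms in cases against controls could show very large differences that look like findings, although they carry no information on whether PDL causes the symptom, since cases and controls all took PDL. And the matched set, which could do useful work on contributing factors, is not expressly given that work. Factors contributing to ADRs are part of the study objective and are named again under the primary outcome.

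**Working it through.** The plan gives no sample size, test or effect size for the case-control part, so there is no figure of its own to reproduce. The check is one of logic, supported by arithmetic on assumed rates.

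**1. Strict reading: symptoms of an ADR.** Every case has at least one event graded positive, probable or possible. No control has one. The proportion with any ADR symptom is 100% in cases and 0% in controls, whatever the data.

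**2. Loose reading, one symptom.** Count any similar symptom, including those graded possibly unrelated in controls. Assume that the drug causes nothing, that the symptom has background prevalence *b*, and that a share *f* of occurrences is graded at least possible. The documents give neither quantity. Then:

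- prevalence in cases = 100%;
- prevalence in controls = b(1 − f) / (1 − bf).

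| b | f = 0.1 | f = 0.5 | f = 0.9 |
|---|---|---|---|
| 1% | 0.9% | 0.5% | 0.1% |
| 5% | 4.5% | 2.6% | 0.5% |
| 10% | 9.1% | 5.3% | 1.1% |

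For example, b = 0.05 and f = 0.5 give 0.025 / 0.975 = 2.6%. So the contrast is 100% against about 0.1% to 9%, with no drug effect at all.

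**3. Loose reading, two symptoms.** Let two independent symptoms each have background *b*, with share *f* graded related, and let a case be anyone with at least one symptom graded related. For the first symptom:

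- in cases: [b − b(1 − f)(1 − bf)] / [1 − (1 − bf)²];
- in controls: b(1 − f) / (1 − bf).

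| b | f | Cases | Controls | Odds ratio |
|---|---|---|---|---|
| 2% | 0.3 | 50.9% | 1.4% | 72 |
| 2% | 0.7 | 50.7% | 0.6% | 168 |
| 5% | 0.3 | 52.1% | 3.6% | 30 |
| 5% | 0.7 | 51.7% | 1.6% | 68 |

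For b = 0.02 and f = 0.3, the case figure is (0.02 − 0.014 × 0.994) / (1 − 0.994²) = 0.006084 / 0.011964 = 50.9%. The true drug effect is nil in every row.

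**4. What a test would show.** Assume 50 cases and 200 controls, with a symptom seen in *k* cases and no controls. The one-sided Fisher p-value is C(50,k) / C(250,k):

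- k = 1: 50/250 = 0.20;
- k = 2: (50 × 49) / (250 × 249) = 0.039;
- k = 10: about 4.7 × 10⁻⁸.

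Small p-values come from the selection rule once a symptom recurs in several cases, but not for a symptom seen once.

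**5. Incidence from the matched set.** With one case and four controls per set, the case share is 1 / (1 + 4) = 20%, fixed by design. ADR incidence, overall or by level of a factor, cannot be read from such a set. The first risk-factor step therefore needs the full cohort.

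**The case against.** The strongest reply is that controls without the outcome are exactly what a nested case-control study uses, and that the study asks which factors contribute to ADRs. Table 2 names days of medication, age and drug combination. On that view the design fits its question and only a purpose clause is badly worded. This stands as regards the design: a reader might infer that the matched set can answer nothing, and the documents do not support that. The wording still needs correcting, because both places say symptoms and neither assigns the matched set to factors.

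A reader might also infer that symptom comparison is the only use intended. Statistical Analysis leans that way by adding risk factors as a further item, but the Abstract has no such separator and moves straight on to influencing factors. The text is silent rather than exclusive.

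Controls are free of ADRs, not necessarily of symptoms. They may have events graded possibly unrelated, and the second form is completed for these too. So it would be wrong to say that symptoms never occur, or are never recorded, in controls. This softens the contrast without removing its cause, as steps 2 and 3 show.

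It would also be too strong to say that any test must be significant: a symptom in 1 of 50 cases and 0 of 200 controls gives p = 0.20. The article names no test for this comparison and does not say it would be read as evidence of causation; attribution rests on the three-level causality review.

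Finally, a fuller protocol or analysis plan may hold more detail. That would excuse an omission, but here a purpose is positively stated, twice, and it does not suit the way the controls are chosen.

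**Conclusion.** The point holds for the stated symptom comparison and goes no further. On the strict reading the contrast is fixed by definition. On the loose reading it mainly reflects selection and causality grading: with no drug effect, the assumed two-symptom scenarios give odds ratios of about 30 to 170. Those sizes rest on assumed background rates, grading shares and independent symptoms; that selection produces a contrast without any drug effect does not depend on the particular values. Since all patients took PDL, neither reading bears on whether PDL causes a symptom.

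The nested case-control design remains sound for factors that precede the ADR. The primary outcome, ADR incidence described in the cohort, is unaffected. This is a correction that should be made before analysis, not a flaw in the study as a whole.

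**What to change.** In the Abstract and in Statistical Analysis, replace the symptom comparison with a statement that the matched sets compare characteristics and exposures preceding ADR onset, such as drug combination, days of medication before onset, allergy history and comorbidity. Use an analysis that respects the matching, for example conditional logistic regression. Describe ADR symptoms among cases only. State that ADR incidence by factor is estimated in the full cohort; this also covers age, gender and batch, whose effects the matching removes from the matched sets.

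The cost is the loss of the case-control symptom contrast and a little added analysis work. No new data are needed, and neither the sample size nor the primary outcome changes.

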### Sample Size

In accordance with the requirements of the *Guide to Key Drug Monitoring for Manufacturing Enterprises* [24], and referring to the 2013 *Technical Specifications for Intensive Hospital Safety Monitoring of Post-Marketing Chinese Medicine* [25], the “rule of threes” was used for sample size calculation, which states that “if no specific event is observed in X existing cases, there is a 95% likelihood that the occurrence rate of such an event is ≤3/X.” Based on the detection rate of rare ADRs (1/10,000 to 1/1000), it is estimated that 3000 cases would need to be collected. However, due to the low probability of ADR occurrences investigated in this study, actual monitoring will be extended to 10,000 cases.

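### Screening factors one at a time on crude ADR incidence before the group LASSO can drop a true risk factor that a confounder masks

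*Protocol article*

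**What the plan says.** The Statistical Analysis section of the protocol article sets out the search for risk factors as an ordered sequence. The opening step, introduced by the word *First*, is that "the differences of ADR incidence among the possible influencing factors will be compared separately to find the factors with large differences". The next sentence reads: "Then, synthetic minority oversampling technique and group least absolute shrinkage and selection operator methods will be used to identify factors", followed by the statement that these are the factors influencing ADR occurrence.

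The Methods part of the abstract repeats the order and puts confounding control at the end: "Finally, propensity scoring methods will be used to control for confounding variables". In the main text, propensity scoring is joined to the LASSO sentence rather than placed after it. In neither place is it part of the crude comparison.

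Table 2 names the candidate factors only by example: "Days of medication, age, drug combination, etc". The article gives no threshold for a difference large enough to count. It does not say that every candidate enters the group LASSO whatever the first step shows.

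**The concern.** Group LASSO is itself a selection method. It looks at all candidates jointly, with a penalty to limit overfitting. A crude comparison placed before it is a second selection, made one factor at a time and without adjustment.

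Two things follow. First, a factor that raises the risk of an ADR, but is less common among patients who carry another strong risk factor, can show little crude difference. If it is dropped at that point, the joint model never sees it. Second, penalty tuning done only within the LASSO step takes no account of the selection already made on the same data.

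Candidates such as age, drug combination, days of medication and allergy history can plausibly be related to one another, and the article itself expects confounding, since it plans propensity scores. Exploring contributing factors is part of the stated objective and is attached to the primary outcome section, so a masked factor lost here is lost from one of the study's intended results.

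**Working it through.** **1. The plan's own figure.** The Sample Size section uses the rule of three at a rate of 1/1000: 3 / 0.001 = 3000. The exact form gives ln(0.05) / ln(1 − 0.001) = 2994, so the statement that "it is estimated that 3000 cases would need to be collected" is reproduced. The point does not depend on it, but the event count matters. Because "actual monitoring will be extended to 10,000 cases", the expected number of cases of one rare ADR is 10,000 × 1/10,000 = 1 to 10,000 × 1/1000 = 10. The article gives no overall ADR rate. I assume about 48, 100 and 200 ADRs, that is 0.48%, 1% and 2% of 10,000.

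**2. How masking works.** Assumed inputs, none of them in the article: factor X with true odds ratio 2; confounder C with odds ratio 3 and prevalence 30%; X present in 10% of patients with C and 40% of those without.
- P(C | X present) = 0.3×0.1 / (0.3×0.1 + 0.7×0.4) = 0.03/0.31 = 0.097
- P(C | X absent) = 0.3×0.9 / (0.3×0.9 + 0.7×0.6) = 0.27/0.69 = 0.391
- For a rare outcome, crude OR ≈ 2 × (1 + 2×0.097) / (1 + 2×0.391) = 2 × 1.194/1.782 = 1.34

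Simulation at about 48 ADRs gave a crude OR of 1.39 and an adjusted OR of 2.08.

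**3. The screen and the LASSO.** The screen columns come from 300 simulated cohorts per setting. The LASSO columns come from 60 per setting, with 20 candidates (X, C and 18 null factors), cross-validated plain LASSO, and a screen at p<0.05.

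| ADRs (about) | X dropped, p<0.05 screen | X dropped, p<0.20 screen | X kept, screen then LASSO | X kept, LASSO alone |
|---|---|---|---|---|
| 48 | 84% | 56% | 13% | 42% |
| 100 | 71% | 49% | 22% | 70% |
| 200 | 45% | 24% | 43% | 98% |

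The columns are consistent: the share kept after the screen never exceeds the share that passes it (16%, 29%, 55%). With 60 runs, the 95% simulation margin on one percentage is at most 1.96 × √(0.25/60) = 13 points. The smallest gap, 42 − 13 = 29 points, has a standard error of about √(0.42×0.58/60 + 0.13×0.87/60) = 7.7 points if the two arms are treated as independent, so simulation noise does not explain it.

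**4. Other settings.** These used 400 runs, 10,000 patients and confounder OR 4, and compared a crude test with a logistic model adjusted for C, both at p<0.05.
- Same negative relation: crude OR ≈ 2 × (1 + 3×0.097)/(1 + 3×0.391) = 1.19 (simulated 1.17 to 1.20). X passes the screen in 9%, 16% and 23% of runs at about 23, 113 and 224 ADRs. The adjusted model detects it in 27%, 88% and 99%.
- No relation between X and C: 39% v 38%, 97% v 96%, and 99.8% v 99.8%, at about 24, 120 and 239 ADRs. The screen costs nothing visible.

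**5. The price of removing the screen.** In the LASSO runs, about 3 to 4.5 of the 18 null factors were selected without the screen, against about 1 with it.

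**The case against.** The strongest reply is that the gate is a reading. A reader might infer that the plan restricts the LASSO to factors that pass the crude step, but the article never says so. It gives the LASSO step the task of identifying factors, and the first step could be the usual univariable table, with the LASSO candidate list left to an analysis plan that is not shown. That stands as a limit. Still, a step whose purpose is to find factors, followed by *Then*, is most naturally taken as a filter. If a descriptive table was meant, the sentence needs the same correction.

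A reader might also infer that the screen does nothing but add error, or that it lets noise factors through. The evidence is against this. Without a screen every null factor reaches the LASSO, and more of them are finally selected (step 5). The screen buys fewer false selections at the price of losing masked true factors.

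Nor does the screen discard confounded factors in general. Positively confounded factors have inflated crude differences and tend to pass. The loss concerns negatively confounded ones.

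Finally, the odds ratios, prevalences, ADR counts and p<0.05 cut-off are all assumed, and the check used plain rather than group LASSO. I make no claim about how the planned oversampling would shift the percentages. They illustrate the mechanism and do not forecast this study.

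**Conclusion.** The point holds in a limited form. On its natural reading, the plan lets unadjusted differences choose which factors go forward. This can remove a true, negatively confounded risk factor that the LASSO alone would more often keep: 13%, 22% and 43% kept against 42%, 70% and 98% at about 48, 100 and 200 ADRs, under the inputs listed. A more lenient cut-off reduces the loss but does not remove it.

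The loss depends on confounding that runs against the factor; without it, the crude and adjusted tests perform alike. It also depends on having enough events. At about 23 ADRs both approaches usually miss the factor, so with 1 to 10 neither can have useful power.

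A reader might infer that the primary result is at risk. It is not: ADR incidence is analysed descriptively and does not pass through this step. What is affected is the exploratory search for contributing factors. The text is worth changing because the change is cheap.

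**What to change.** In the Statistical Analysis section and the abstract, state that the one-at-a-time comparisons are a descriptive table only and do not decide entry to the model. Then state what enters the group LASSO:

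- all prespecified pre-treatment candidates, that is the baseline items of Table 1. Adverse reaction occurrence must be left out because it is the outcome, and post-treatment laboratory results because they may be consequences or components of an ADR;
- exposure factors measured before ADR onset, namely days of medication and drug combination. Table 1 records drug combination only at the visits after the start of treatment, so its timing relative to onset has to be fixed.

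Tune the penalty by cross-validation assessed on original patients, not on synthetic records. If a screen is kept, run it inside the resampling loop so that tuning reflects it.

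The cost is a short change to the text and no new data. The small downside is that more null factors may be selected, so report how stable each selection is across resamples and label the results exploratory.
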